#### The 6-Minute Walking Test

The submaximal exercise 6MWT, which entails the measurement of the distance walked over a span of 6 minutes, will be performed according to the detailed protocol used in the respective medical centers. The blood pressure (BP), heart rate (HR), and SpO_2_ will be measured directly before and after the test. The following will be recorded: whether the patient completed the test, the distance walked (m), SpO_2_, the SpO_2_ nadir, and dyspnea sensation measured with the Modified Borg Scale and the Visual Analogue Scale (VAS). If the test is stopped or paused before 6 minutes, the reason (eg, dyspnea, high BP, cardiac arrythmia, limb pain, angina, or other) will be recorded.

The 6MWT will be performed according to Polish Respiratory Society guidelines [10]. Participants will be informed at 30-second intervals about the amount of time remaining. The predicted distance will be calculated based on the equation published in Polish Respiratory Society guidelines for the interpretation of the 6MWT as the most accurate for participants’ characteristics [10].

Pulse oximetry will be performed for all patients. If SpO_2_<92% or there are clinical indications for oxygen therapy, ABG analysis will be performed. For ABG analysis, an artery (radial or femoral) is punctured in order to take a sample of arterial blood. The artery is then compressed in order to prevent bleeding/hematoma. The procedure is performed according to ERS guidelines [11].

#### Computed Tomography

HRCT of the lung will be performed during hospitalization. If the patient provides a CT scan from up to 6 months prior to recruitment (eg, from the outpatient clinic), we will analyze both scans and the radiological descriptions. To ensure the patient’s anonymity, a CD containing the patient’s scans will be marked by the technician according to the aforementioned pattern. Radiological analysis will be performed using the OsiriXLite DICOM Viewer. The following densitometric values will be measured: mean lung attenuation (MLA), kurtosis, skewness, and deviation of lung radiodensity (SD_IR_). Statistical analysis of the data will be performed using Statistica software. Data will be presented as the median value and IQRs. Differences between quantitative data will be analyzed using the Kruskal-Wallis test and the post hoc Dunn test.

#### Transthoracic Echocardiography

TTE with a thorough right heart description will be performed. The following parameters will be noted in the patient’s medical file: main pulmonary artery diameter; acceleration time; pulmonary valve peak velocity, tricuspid annular peak systolic velocity (TAPSV), tricuspid annular plate systolic excursion (TAPSE), and tricuspid valve peak regurgitation velocity; right ventricular basal and right ventricular midcavity diameters; right ventricular outflow tract and proximal and distal right ventricular outflow; right atrial short- and long-axis, inferior vena cava, and superior vena cava diameters; and right ventricular wall thickness.

Rheumatological consultation will be provided to patients with IPAF and CTD-ILD to verify the diagnosis.

#### Choice of Candidate IPAF Biomarkers

KL-6 (mucin 1) is a glycoprotein encoded by the *MUC1* gene and is expressed on the outer surface of type II alveolar epithelial cells and the airway epithelium. It has been proposed as a biomarker of IPF [12]. KL-6 probably promotes fibroblasts’ migration, proliferation, and survival in the respiratory system [12]. High serum KL-6 levels have been found in patients with IPF, NSIP, and other ILDs [13-15], which is associated with an aggressive clinical course and could also serve as a predictor of acute exacerbation [16]. High KL-6 levels have also been found in the BALF of individuals with various ILDs, including IPF [17].

Another proposed ILD activity biomarker is CC-chemokine ligand (CCL)18. In a population of patients with idiopathic ILD and SSc, it was revealed that the BALF CCL18 level was negatively correlated with the TLC and the DLCO and positively correlated with BALF neutrophil and eosinophil cell counts. During the follow-up period of ≥6 months, a negative correlation was observed between the decrease in the predicted TLC and the increase in serum CCL18 levels [18]. We hypothesize that such correlation also exists in IPAF, and we will test the theory that patients with IPAF with autoantibodies associated with SSc (anti-PmScl) have higher serum or BALF CCL18 levels than those who test negative for these autoantibodies.

Surfactant proteins SP-A and SP-D are large hydrophilic molecules produced by Clara cells and type II alveolar epithelial cells. SP-A and SP-D play an important role in innate immunity and modulate the excessive inflammatory response on the alveolar surface [19-21]. SP-A and SP-D levels are higher in patients with IPAF than in healthy individuals, patients with infectious pneumonia, or patients with nonfibrotic lung diseases [22-24]. Moreover, serum SP-D levels are lower in the IIP non-IPF group than in the IPAF group [22]. SP-A levels cannot be used to differentiate between patients with IPAF and CTD-ILD [24].

According to Xue et al [22], a negative correlation of serum SP-A levels and the DLCO was revealed in the IIP group (which included 27/69 patients with IPAF, although this subgroup was not separately analyzed). A negative correlation was also revealed with FEV_1_ and the FVC [22]. This conclusion was partially confirmed by Wang et al [23], who revealed a negative correlation between serum SP-A levels and changes in the DLCO, FEV_1_, and FVC values after treatment. Additionally, Wang et al [23] suggested a prognostic role of SP-A: the pretreatment levels were found to be significantly lower than the posttreatment ones in individuals with progressive fibrosis during the course of IPAF. Moreover, a positive correlation was found between shifts in KL-6 and SP-A levels [23]. In a prospective study, Xue et al [24] observed a significant difference in serum SP-A levels measured at baseline and after 1-year follow-up. In individuals whose condition had exacerbated, SP-A levels were correlated with lung involvement scores on HRCT [24].

These findings need to be validated in European populations. There is a need to determine whether there is a correlation between lung involvement and a decrease in pulmonary function and SP-A/SP-D levels in the bodily fluids of patients with IPAF.

CHIT1 is a member of the glycosyl hydrolase family 18. It is expressed predominantly in polarized and differentiated macrophages and acts as an innate immune mediator digesting cell walls of pathogens that contain chitin (eg, fungi). CHIT1, due to its dysregulated activity, is a proposed marker in granulomatous and fibrotic ILDs associated with interstitial inflammation and lung tissue remodeling.

A study by Bargagli et al [25] revealed elevated CHIT1 activity in the BALF of individuals with IPF in comparison with the healthy control group; however, no significant differences in the serum levels were noted. This suggests the role of CHIT1 expression in interstitial macrophages in tissue injury and remodeling. We hypothesize that CHIT1 may play an important role in the pathogenesis of other ILDs, including IPAF, especially with a progressive fibrosing phenotype.

Lee et al [26] revealed that in 2 different cohorts of individuals with SSc, CHIT1 activity and concentrations increased in the serum and BALF compared to demographically matched healthy controls. Individuals with SSc-ILD, in comparison with patients without lung involvement, were characterized by higher CHIT1 serum activity, which was also correlated with disease severity. The authors revealed that CHIT1 upregulates transforming growth factor beta 1 (TGF-β1) receptor expression and its signaling in fibroblasts, which makes CHIT1 a modulator of progressive interstitial lung fibrosis [27].

These findings raise the question whether CHIT1 or TGF-β1 and their interaction could be a potential target for SSc pharmacological therapy. As the etiopathogenesis of IPAF is still obscure, we plan to analyze both circulatory and lung activities of the enzyme to establish its potential role in the disease pathogenesis.

S100A9, also referred to as myeloid-related protein 14 or calgranulin B, is a member of the calcium-binding protein S100 family and is mostly expressed in neutrophils but also on vascular endothelial cells and mature macrophages. S1009A expression is enhanced by some chronic inflammatory factors [28]. It acts as an immunomodulatory, proinflammatory, and profibrotic agent [29]. It is mostly secreted in inflammatory lesions [30], and it has been suggested as a potential target for IPF treatment [31] and as a candidate biomarker to differentiate between IPF and other fibrotic ILDs [32]. However, convincing evidence from contemporary trials is yet scarce.

Elevated serum S100A9 levels have been reported in samples obtained from patients with RA, SLE, SSc, vasculitis, lung cancer, and various other diseases associated with chronic inflammation [33-35]. It has also been demonstrated that S1009A may promote atherosclerosis [36]. In an observational study by Lin et al [37], it was revealed that S100A9 levels were significantly elevated in BALF samples obtained from patients with severe IPF. It has also been demonstrated that S100A9 levels in the BALF of patients with IPF are positively correlated with the percentage of BALF neutrophils. This suggests a relationship between S1009A levels and disease activity. Some studies have reported that BALF S100A9 levels are significantly elevated in individuals with pulmonary involvement during the course of SSc [38,39].

CCL2 is a protein that attracts T lymphocytes, natural killer lymphocytes, and fibrocytes [40]. It is associated with inflammatory processes, cell migration and activation, fibrosis, and angiogenesis [41] through its 7-transmembrane-spanning G-protein-coupled CC-chemokine receptor 2 [42]. CCL2 plays a significant role in the pathogenesis of various diseases, such as tuberculosis [43], asthma [44], and RA [45].

A connection was established between CCL2 polymorphism and the occurrence of autoimmune disorders. The *CCL2* gene (–2518G/A) single-nucleotide polymorphism has been shown to be associated with sarcoidosis [46]. Increased CCL2 levels have been found in the serum and BALF of patients with IPF [47]. In vitro and in vivo studies have revealed that CCL2 is associated with fibrosis by supporting monocyte-/macrophage-mediated inflammation, angiogenesis, collagen synthesis, myofibroblast cell differentiation, and fibroblast activation [48].

It remains unclear whether the chemokine profile of serum and BALF of individuals with IPAF, especially patients with progressive fibrosis, resembles that of patients with IPF.

### Data Collection

Data will be collected via questionnaires: the Leicester Cough Questionnaire, St. George’s Respiratory Questionnaire, the Fatigue Assessment Score and 36-item Short Form (SF-36) v.2 Quality of Life Questionnaire, the HADS-M, and the PHQ-9. To help unify data and due to copyright reasons, surveys for physicians will be set up on servers of the Medical University of Silesia. All the aforementioned documents will be provided to the patients in their native tongue and have been validated in the Polish population.

### Statistical Analysis

Statistical tests will be chosen due to variable distribution. To verify the normality of variable distribution, the Shapiro-Wilk test will be performed. To compare parameters between the 1 study and 2 control groups, ANOVA or the Kruskal-Wallis test will be performed (for normal or nonnormal variable distribution, respectively). To correlate the variables, Pearson or Spearman correlation tests will be performed (for normal or nonnormal variable distribution, respectively). To determine the relationship between variables, the linear regression test will be performed.

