### Study Design

#### Phase 1

All patients meeting the inclusion criteria and not meeting the exclusion criteria regardless of prior treatment history will be recruited to phase 1 of the study. The recruitment process duration is estimated at 12 months. The previous recruitment of 40 patients led to a pilot study [7], which impacted further study design. The maximum number of patients included in this phase will be 80 (33.3%) in the IPAF group, 80 (33.3%) in the CTD-ILD group, and 80 (33.3%) in the IIP group.

#### Phase 2

Only patients with newly diagnosed disease (eg, no prior diagnosis of ILD and, hence, no prior treatment) will be recruited. The estimated recruitment duration is 36 months. The number of patients to be included in this phase will be 20 (33.3%) in the IPAF group, 20 (33.3%) in the CTD-ILD group (only those with RA, SSc, PM/DM), and 20 (33.3%) in the IIP group (only those with IPF, NSIP, COP, LIP; optimally 10, 50%, patients in the IPF subgroup and 10, 50%, in the non-IPF subgroup). Patients who were previously recruited to phase 1 of the study and meet the inclusion criteria of phase 2 may also be included.

Please see Figure 2 for a flowchart of the study design.

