A practical question we are going to face stems from the fact that instructions for most ELISA kits that are available for research use in our area only contain suggestions/guidelines for serum dilution. Therefore, we will need to either predict the levels of the aforementioned proteins in BALF or experiment with dilution. As we are unsure how much time it will take to recruit the adequate number of individuals, we plan to perform a miniexperiment beforehand: First, we will test the serum according to the manufacturer’s guidelines. If the standard 1:40 dilution does not lead to the detection of predicted concentrations, we will check the 1:20 dilution, 1:5 dilution, and undiluted samples. The next step will be testing BAL samples. We will test 1:20 dilution samples, and again, if this does not result in the detection of protein concentrations within the range provided in the kit instruction, we will test the 1:5 dilution and undiluted specimens.

The clinical stability of IPAF is an important subject, as the development of mild extrapulmonary symptoms may be overlooked. In our opinion, this specific population requires above-average clinical vigilance due to the fact that reclassification as definite CTD-ILD prompts a change in the therapeutic approach based on ACR/EULAR guidelines. This is why we plan to cooperate closely with rheumatologists regarding assessment of the extrapulmonary manifestations of autoimmunity. However, there is also a possibility that an entity that had been initially classified as idiopathic ILD may later be reclassified as IPAF. To test this hypothesis, we plan periodic rheumatological revaluations of this subgroup, together with retesting for ANAs (serological domain of IPAF).

Data on the progression of IPAF to CTDs are scarce and conflicting. Scirè et al [53] reported that 42% of patients with IPAF with antisynthetase antibody positivity were ultimately reclassified as RA-ILD, PM/DM-ILD, or myositis-RA overlap syndrome. Ito et al [54] also reported that 12.2% of individuals meeting IPAF serological and morphological criteria were diagnosed with CTD during a median follow-up period of 54 months. However, Chartrand et al [55] found that none of the 56 individuals with IPAF was rediagnosed over a follow-up period of 48 months.

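### Test choice rests on a normality pretest that ignores unequal spread: near-nominal error at the planned equal sizes, but not if groups or subgroups turn out unequal in both size and spread

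*Protocol article*

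**What the plan says.** The rule is in the Statistical Analysis section: "Statistical tests will be chosen due to variable distribution". The gate is named: "To verify the normality of variable distribution, the Shapiro-Wilk test will be performed". For the three-group comparison, "ANOVA or the Kruskal-Wallis test will be performed (for normal or nonnormal variable distribution, respectively"). For associations, "Pearson or Spearman correlation tests will be performed (for normal or nonnormal variable distribution, respectively"). Variance plays no part in the choice. The level of the pretest, and whether it is applied to each group, to residuals or to pooled values, are not stated.

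Group sizes are in Study Design. In phase 1, "The maximum number of patients included in this phase will be 80 (33.3%) in the IPAF group", with the same cap for CTD-ILD and IIP. In phase 2, "The number of patients to be included in this phase will be 20 (33.3%) in the IPAF group", again with the same number in the other two groups.

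CT densitometry has its own provision under Computed Tomography: "Differences between quantitative data will be analyzed using the Kruskal-Wallis test and the post hoc Dunn test".

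**The concern.** Normality is the wrong property to gate on. When group sizes differ, classical ANOVA is distorted mainly by unequal variances, and Kruskal-Wallis is also affected by them. A Shapiro-Wilk result says nothing about that, so the rule can send a variable to either test without protection.

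Unequal sizes are plausible although not planned. The phase 1 numbers are maxima, and in the Discussion (Summary) the authors write that "we are unsure how much time it will take to recruit the adequate number of individuals". Several planned contrasts have no planned balance: anti-PmScl-positive against negative IPAF (Choice of Candidate IPAF Biomarkers), UIP-RA against UIP-IPAF (Discussion, Summary), and RA-ILD, SSc-ILD or PM/DM-ILD against matching IPAF subgroups (Impact of Pilot Study Results on the Protocol).

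A second issue does not depend on unequal spread. The Abstract plans a comparison of serum and BALF cytokine levels, and biomarker blood sampling is repeated at visits 3 to 5. If the pretest decides each time, one marker can be analysed by means in one place and by ranks in another. Pearson and Spearman likewise measure different things, so the reported quantity would depend on the pretest.

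**Working it through.** The document gives no alpha, SD, effect size or sample-size derivation, so there is no stated figure to reproduce.

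**Inputs from the protocol.** The rule as quoted; 80/80/80 as the phase 1 maximum; 20/20/20 in phase 2.

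**Assumptions.** Alpha 0.05 for both the pretest and the main test; IPAF-to-control SD ratio r between 0.5 and 2; achieved IPAF size 40 or 20 against 80/80 if the cap is missed.

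**Why size and spread interact.** With no true difference and k = 3 groups, N patients in all:
- E(MS between) = Σ(1 − nᵢ/N)σᵢ² / (k − 1)
- E(MS within) = Σ(nᵢ − 1)σᵢ² / (N − k)

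Classical ANOVA needs their ratio to be 1.
- Equal sizes: both equal the mean of the three variances, so the ratio is 1 whatever the spread.
- 40/80/80, r = 2: between = (0.8×4 + 0.6 + 0.6)/2 = 2.20; within = (39×4 + 79 + 79)/197 = 1.594; ratio 1.38.
- 20/80/80, r = 2: between = (0.889×4 + 0.556 + 0.556)/2 = 2.333; within = (19×4 + 79 + 79)/177 = 1.322; ratio 1.77.
- 40/80/80, r = 0.5: between = (0.8×0.25 + 1.2)/2 = 0.70; within = (39×0.25 + 158)/197 = 0.852; ratio 0.82.

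A ratio above 1 gives too many false positives. A ratio below 1 gives too few.

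**Simulated type I error of the two-stage rule.** Normal data, no true difference, 2,500 runs per cell (3,000 for r below 1). Standard error at 0.05 is √(0.05×0.95/2500) ≈ 0.004. The main figure is for a per-group pretest; brackets give the range when the pretest is applied per group, to residuals or to pooled values.

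| Sizes | r | Type I error |
|---|---|---|
| all simulated sizes | 1 | 0.047-0.056 (0.044-0.056) |
| 80/80/80 | 2 | 0.063 (0.056-0.068) |
| 20/20/20 | 2 | 0.062 (0.049-0.068) |
| 40/80/80 | 1.5 | 0.084 (0.071-0.084) |
| 40/80/80 | 2 | 0.114 (0.082-0.114) |
| 20/80/80 | 1.5 | 0.109 (0.101-0.109) |
| 20/80/80 | 2 | 0.167 (0.110-0.167) |
| 40/80/80 | 0.5-0.67 | 0.036-0.038 |
| 20/80/80 | 0.5-0.67 | 0.027-0.030 |

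A separate simulation gave about 8-12% at 40/80/80 and 10-19% at 20/80/80 for r of 1.5 to 2. Those rounded ranges are used in the conclusion.

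Kruskal-Wallis alone is not protected: 0.090 at 20/80/80 with r = 2. Welch ANOVA on normal data stayed between 0.042 and 0.058 in the equal-spread and larger-spread cells. On untransformed lognormal data with equal means and a log-SD ratio of 1.5 to 2, Welch itself gave 0.063-0.129, so the scale has to be fixed as well as the test.

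**Method switching.** For two independent samples of one lognormal marker (2,000 runs), the rule chose different tests in 31-47% of runs at 20 per group for log-SD 0.1 to 0.3. At 80 per group the figures were 48%, 26% and 2% for log-SD 0.1, 0.2 and 0.3. At log-SD 0.5 they were 19% at 20 per group and none at 80. Serum and BALF from the same patients are not independent, so these figures only indicate the scale.

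**The case against.** The strongest reply is that the inflation needs a condition the plan does not contain. Groups are planned equal, no SDs are given, and the phase 2 figure of 20 is a stated number, not a maximum. At those sizes the error rate is close to nominal. If the smaller group were the less variable one, the rule would be conservative. All of this stands, and the point is therefore conditional.

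A reader might infer that the Shapiro-Wilk step itself inflates the error rate. It does not: with equal SDs the two-stage rule holds at about 5% at every size simulated. The inflation comes from unequal spread combined with unequal size and would remain without the pretest.

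A reader might also see the CT provision as contradicting the general rule. It is a specific provision for one set of variables and fixes the test in advance, which is what is asked for here. Nor does the text say that linear regression will be applied to every variable or to untransformed ELISA values. It says only that regression will examine relationships between variables.

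It can be argued that the ANOVA variant, the pretest unit and any transformation belong in a fuller analysis plan. That is fair for those details. But the article itself commits to choosing the test from the data, and that rule can be judged as written.

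The stakes are limited: the stated primary purpose concerns incidence, and no confirmatory test or alpha is declared. Pearson against Spearman was not simulated; the objection there is to comparability, not to an error rate.

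Log-scale Welch is also not free. With heavy-tailed log values (t, 3 df) its power was 0.66 against about 0.87 for the protocol's rule at 80 per group, and 0.62 against 0.78 at 20. For exactly lognormal markers (log-SD 0.4-0.8, 80 per group) it lost nothing: 0.84-0.85 against 0.82-0.83.

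**Conclusion.** The concern holds in a limited, conditional form. At the planned equal sizes the rule is near nominal, about 5-7% for SD ratios up to 2. If achieved groups are unequal and the smaller one is 1.5 to 2 times as variable, type I error is about 8-12% at 40/80/80 and 10-19% at 20/80/80, towards the lower end or slightly below it if residuals or pooled values are pretested. If the smaller group has half the spread, it is about 3-4%. The documents do not say which direction applies. These figures rest on assumed SD ratios, an assumed shortfall, alpha 0.05 and normal data. They are for three groups; the two-group subgroup contrasts were not simulated, though a pooled variance works the same way there.

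The loss of comparability across fluids and visits needs no unequal spread. It matters for mildly skewed markers and small groups; strongly skewed markers at 80 per group go to Kruskal-Wallis almost every time.

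**What to change.** In the Statistical Analysis section:
- Replace classical ANOVA with Welch ANOVA, and use Welch contrasts for pairwise comparisons.
- Fix one method and one scale per variable family before the data are seen. For example, analyse ELISA markers on the log scale with Kruskal-Wallis as the sensitivity analysis, and use Spearman for all biomarker correlations.
- Use Shapiro-Wilk for description only.

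The pre-specified Kruskal-Wallis and Dunn tests for CT values can stay.

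The cost is a few sentences of wording; standard software covers all of it. Marker results would be reported as geometric mean ratios. Log-scale Welch loses power against a rank test if log values are heavy-tailed, which is why the rank test is kept alongside.

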**Objective:**

This study aims to determine the characteristics of Polish patients with IPAF, compare them with patients with other interstitial pneumonias, and search for the prognostic and diagnostic biomarkers of IPAF in serum and bronchoalveolar lavage fluid (BALF).

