### Objectives

The primary purpose of this study is to determine the incidence of IPAF in comparison with IIPs and ILDs occurring during the course of autoimmune diseases in 6 Polish pulmonological centers. Further objectives of this study include determination of the clinical, serological, functional, radiological, and histopathological characteristics of patients with IPAF; analysis of diagnostic strategies for specific IPAF subgroups; determination of the potential diagnostic, predictive, and prognostic features of IPAF; and prospective 5-year assessment of patients with IPAF in order to determine the stability of the diagnosis and potential progression to other diseases (eg, CTDs). Please see Figure 1 for the study protocol. To the best of our knowledge, this is the first prospective study focused on patients with IPAF, CTD-ILD, and IIP in Eastern Europe.

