### Impact of Pilot Study Results on the Protocol

In our pilot study [7], we revealed a greater prevalence of gastrointestinal reflux disease (GERD) in the CTD-ILD group than in the IPAF and IIP groups. Data on the impact of GERD on fibrosis pathogenesis are conflicting. There are data suggesting that exposure of the interstitial tissue to a low pH results in repeated lesions and, consequently, progressive fibrosis. However, there are also data supporting a hypothesis that GERD actually results from progressive fibrosis and a shift in intrathoracic pressure due to altered anatomy. Therefore, we decided to launch a substudy on patients with progressive fibrosing ILD (PF-ILD), focusing on the impact of GERD on the disease course. We will monitor 24-hour impedance-pH to objectify GERD episodes and correlate them with symptoms.

In the pilot study [7], it was also revealed that BALF levels of interleukin 8 (IL-8), CXCL1, and TGF-β1 were significantly higher in the CTD-ILD group than in the IPAF and IIP groups. We hope that the analysis of 240 subjects in this full-size study will reveal more defined differences between study groups. We plan to analyze subgroups (eg, RA-ILD or SSc-ILD) and compare them with their IPAF counterparts (based on the presence of clinical symptoms and specific autoantibodies). We also plan to distinguish an IPAF subgroup associated with the presence of antisynthetase autoantibodies and compare it with the PM/DM-ILD subgroup in terms of clinical stability and outcomes.

Our pilot study [7] also revealed that the BALF IL-8 concentration is associated with the presence of skin teleangiectasias. IL-8 is a known proangiogenic factor. In this full-size study, we plan to perform videocapillaroscopy to stratify participants according to the Cutolo nailfold capillaroscopy classification and measure the concentration of proangiogenic cytokines in both serum and BALF. We will be able to compare corresponding Cutolo subgroups of SSc-ILD and IPAF and determine the impact of proangiogenic factors on pathological angiogenesis.

We also hypothesize that there will be significant intergroup differences between the reported severity of cough and dyspnea as well as psychological symptoms and their impact on various aspects of the QoL.

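### The only between-group test stated for the serum and BALF markers is a three-group omnibus test, which does not show from which control group IPAF differs, or how well a marker discriminates

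*Protocol article*

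**What the plan says.** The Abstract's Objective commits the study to looking for markers in serum and BALF that are diagnostic or prognostic for IPAF. The Objectives section repeats the aim as "determination of the potential diagnostic, predictive, and prognostic features of IPAF".

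The Statistical Analysis section names three kinds of method:

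- Group comparison: "To compare parameters between the 1 study and 2 control groups, ANOVA or the Kruskal-Wallis test will be performed", with the choice depending on normality.
- Correlation: "To correlate the variables, Pearson or Spearman correlation tests will be performed".
- Regression: "To determine the relationship between variables, the linear regression test will be performed", with no outcome or predictor named.

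A pairwise step appears once, in the Computed Tomography section, for the densitometric values: "Differences between quantitative data will be analyzed using the Kruskal-Wallis test and the post hoc Dunn test". It is not carried over to the biomarkers.

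The section on the impact of the pilot study reports that BALF IL-8, CXCL1 and TGF-β1 "were significantly higher in the CTD-ILD group than in the IPAF and IIP groups". The Abstract's Methods keep these three markers in the full study. For group size, the Phase 1 paragraph says "The maximum number of patients included in this phase will be 80 (33.3%) in the IPAF group, 80 (33.3%) in the CTD-ILD group", and the same maximum for IIP.

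**The concern.** A marker is diagnostic of IPAF only relative to a comparator. The clinically distinct questions are whether it tells IPAF from CTD-ILD and whether it tells IPAF from IIP. The article's own background treats them as distinct: it reports that SP-A does not separate IPAF from CTD-ILD, while serum SP-D differs between IPAF and non-IPF IIP.

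The omnibus test has one null, that all three groups are alike. It can reject when IPAF equals one control group, or when it lies between the two. A p-value also says nothing about how well a marker classifies patients. If the stated method is followed literally, the diagnostic aim goes unanswered, and a marker that only sets CTD-ILD apart gives the same significant result as one that sets IPAF apart.

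**Working it through.** **Inputs from the article.** Three groups, up to 80 each in phase 1 (80 + 80 + 80 = 240, which agrees with the stated total) and 20 each in phase 2. The pilot pattern has CTD-ILD as the outlying group, with no difference between IPAF and IIP reported.

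**Inputs assumed, because the article gives none.** Two-sided alpha 0.05, normal data, common SD of 1, shifts of 0.3 to 0.8 SD. The article gives no power or effect-size figure to reproduce.

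**1. Pilot-like pattern: IPAF = IIP, CTD-ILD shifted by 0.5 SD, 80 per group.**

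- ANOVA noncentrality is λ = n Σ(μᵢ − μ̄)². With means 0, 0.5 and 0, μ̄ = 1/6 and the squared deviations sum to 1/36 + 4/36 + 1/36 = 1/6. So λ = 80/6 = 13.3 on (2, 237) degrees of freedom, and power is 91%.
- Kruskal-Wallis, by simulation (3,000 or more studies per scenario), rejects 89-90% of the time.
- Pairwise discrimination for normal data is AUC = Φ(d/√2). IPAF v CTD-ILD: Φ(0.5/1.414) = Φ(0.354) = 0.64. IPAF v IIP: Φ(0) = 0.50.

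**2. What the two contrasts show in the same pattern** (Mann-Whitney, each at 0.05/2 = 0.025):

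| CTD-ILD shift | Kruskal-Wallis rejects | IPAF v CTD-ILD rejects | IPAF v IIP rejects | AUC, IPAF v CTD-ILD |
|---|---|---|---|---|
| 0.3 SD | 47% | 34% | 2.5-3% | 0.58 |
| 0.5 SD | 89-90% | 79% | 2.5-3% | 0.64 |

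The omnibus result mostly reflects a real difference between IPAF and CTD-ILD. It does not show that this is the difference found, nor that IPAF and IIP are not separated.

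**3. IPAF midway between two controls 0.5 SD apart, 80 per group.** Kruskal-Wallis rejects 80% of the time. In 43% of all simulated studies it is significant while neither IPAF contrast is (Dunn test, Bonferroni over three pairs). Each IPAF contrast here is 0.25 SD, so AUC = Φ(0.25/1.414) = 0.57.

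**4. Significance against discrimination.** With 80 per group and one group shifted, the ANOVA reaches 80% power at 0.43 SD. That is a pairwise AUC of Φ(0.43/1.414) = 0.62.

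**5. With 20 per group.** In the pilot-like pattern Kruskal-Wallis rejects 32% of the time at 0.5 SD and 69% at 0.8 SD. The ambiguity is the same, with less power.

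**The case against.** Several points on the other side are sound.

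- A three-group ANOVA or Kruskal-Wallis test is a valid and usual first step, and the quoted sentence does not itself mention diagnosis. This stands. The fault lies in the fit between the stated method and the stated aim.
- This is a condensed article. Post hoc contrasts and an ROC analysis may be in a full protocol or analysis plan that is not shown, so their absence alone is no error. This also stands. What remains is that the article does fix a pairwise step for CT densitometry, while for the biomarkers it fixes only the omnibus test.
- A reader might infer that the omnibus test rejects when only the two control groups differ. That cannot happen: if CTD-ILD and IIP differ, IPAF differs from at least one of them. For the same reason the 89-90% is not a false-positive rate, because IPAF v CTD-ILD is a true difference in that scenario.
- A reader might also infer that the investigators will present markers of established CTD as IPAF markers. The article does not say so. It reports the pilot result by group and direction, and it plans further subgroup comparisons of IPAF with RA-ILD, SSc-ILD and PM/DM-ILD.
- The aim is exploratory, since the wording speaks of a search and of potential features. A fixed AUC threshold would therefore ask too much, and none is proposed here.

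**Conclusion.** The point holds as a mismatch between aim and method, and it is worth correcting. It does not make the study invalid. As written, the only between-group test for the serum and BALF markers does not locate IPAF relative to each control group and gives no measure of discrimination. Correlation and an unspecified linear regression do not fill that gap.

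At 80 per group and a 0.5 SD shift in CTD-ILD alone, a significant omnibus result is expected about nine times in ten. It would accompany modest discrimination from CTD-ILD (AUC 0.64) and none from IIP (AUC 0.50). These figures depend on the assumed alpha, normality and shift, and on reaching the maximum group size. The logical point does not depend on them.

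**What to change.** In the Statistical Analysis section, extend the approach of the Computed Tomography section to every serum and BALF marker:

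- Specify two contrasts, IPAF v CTD-ILD and IPAF v IIP, with multiplicity adjustment (Dunnett after ANOVA, adjusted Dunn after Kruskal-Wallis).
- Report the ROC AUC with 95% CI for each contrast.
- Base any statement that a marker is diagnostic on these results, naming the comparator, and not on the omnibus p-value.

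No AUC cut-off is needed. No further patients or samples are needed, and the article places the start of phase 1 recruitment in the future.

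The cost is slightly more analysis and fewer markers called diagnostic. As a guide, if IPAF itself is shifted by 0.5 SD from both controls with 80 per group, Kruskal-Wallis rejects 90% of the time, but both IPAF contrasts are significant in only 61% of studies (99% at 0.8 SD). Those two figures use a Bonferroni correction over three pairs after a significant Kruskal-Wallis test, which is stricter than adjusting for two contrasts. They apply only to a claim against both comparators; a claim against one needs only that contrast.
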